## **10.QUALITY ASSURANCE**

The investigators will generate, document, and report the trial in compliance with the protocol, GCP guideline, and applicable national and international (US NIH) regulatory requirements. External

monitors may do technical audits, before, during, and after completion of the trial. This will include reviewing the research protocol, operations manual, standard operating procedures, and training materials before initiation of the trial. The site investigators will make study documents and pertinent records readily available for inspection by the local IRB and site monitors. The study sponsor may conduct monitoring or auditing of study activities to ensure the scientific integrity of the study and to ensure the rights and protection of study participants. Monitoring and auditing activities may be conducted by the sponsor (internal), authorized representatives of the sponsor (external) or both. Monitoring or auditing may be performed by means of on-site visits to the Investigators' facilities or through other communications such as telephone calls or written correspondence. The visits will be scheduled at mutually agreeable times, and the frequency of visits will be at the discretion of the sponsor. During the visit, any study-related materials may be reviewed and the Investigators along with study healthcare providers will be available for discussion of finding. The study may also be subject to inspection by regulatory authorities (national or foreign) as well as the IRBs to review compliance and regulatory requirements. Given that the study is neither dictating the need for or treatment of TB diagnosed by the screening, serious adverse events (SAEs) will not be directly attributable to the study.

## **11. STUDY ASSESSMENT AND DISCONTINUATION**

### **11.1. Participant discontinuation**

- There will be premature study discontinuation if there is:
- Refusal of study participants to participate in all components of the study;
- A request by the participants to withdraw;
- A request from the healthcare providers if s/he thinks the study is no longer in the best interest of the participants; or
- At the discretion of the IRB/Ethics Committee, regulatory bodies, sponsor or consensus of the investigators.

### **11.2. Unexpected or adverse events**

Given that the study is neither dictating the need for treatment of TB or specific regimen, serious adverse events will not be directly attributable to the study. The study will not dictate diagnosis or treatment algorithms for TB, and all diagnoses testing assays and treatment regimens will follow the Ethiopian national guidelines; thus, it will not introduce or prescribe new drugs. The major risks of this screening program are related only to pill-taking mechanisms. Both adverse events and serious adverse events will be reported to the EFDA in line with the stipulated timeline irrespective of relatedness to

the study procedure. Adverse reactions to TB medications will not be considered the outcomes of the study. The investigators will capture these events only to the extent they are available in the study health facilities' records and registries. The investigators will conduct chart abstractions to review adverse events that are related to TB treatment, as recorded from the TB clinic registries. For patients who are co-infected with HIV, the chart review will also include the type of HIV regimens, viral load, CD4 counts, and other co-infections diagnosed and treated.

Regarding TB diagnosis, at the initial stage or following the intensive phase, there could be discrepancies between the health facility results (Smear microscopy or Xpert MTB/RIF) and the study result (MGIT liquid culture). In this case, the investigators will communicate the results to the healthcare providers for their review and decision.

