For the control arm, in addition to monitoring medication adherence, a separate secondary analysis will be conducted for any doses that are self-administered after approval from their provider to determine if this approach has an impact on other outcome measures. This will be to determine the real-world practice of in-person DOT where some doses might be self-administered when the provider approved this procedure for extenuating circumstances.

The participants will have IsoScreen™ urine isoniazid test every 15 days, which is a colorimetric assay, whereby the pyridine ring structure of isoniazid and its metabolites is broken by the biochemical reaction leaving it vulnerable to attachment by the condensing agent, barbituric acid.

At the end of the intensive phase, trained research experts will complete several data instruments for all participants. The first is a self-report of medication adherence that the experts will administer. The second is a case report form for which data will be extracted from TB registration logs and participants' charts, focusing on overall treatment outcomes and side effects. For the third instrument, the experts will administer the EuroQol's EQ-5D-5L HRQoL questionnaire to all participants. The experts will also assess patients' costs using the Tool to Estimate Patients' Costs. Then the experts will administer the TSQM version 1.4 tool to determine treatment satisfaction. Finally, the experts will administer the 18-item tool to determine user performance of the MERM device for intervention participants. Following the collection of data from participants, the study investigators will collect qualitative and quantitative data from the providers to learn more about the usability and acceptability of the intervention from providers and the healthcare system perspectives. The investigators will follow-up and capture ongoing data on the status of each pillbox, thus from the distribution of the pillboxes to end of data collection.

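### Adverse reactions are taken passively from clinic records in arms with about 43 versus 4 scheduled contacts, so short or mild events may be under-detected under self-administration

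*Protocol*

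**What the plan says.** Protocol Section 11.2 makes five statements that bear on this:

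- Reporting: "Both adverse events and serious adverse events will be reported to the EFDA in line with the stipulated timeline irrespective of relatedness".
- Status: "Adverse reactions to TB medications will not be considered the outcomes of the study".
- Capture: the investigators take these events "only to the extent they are available in the study health facilities' records and registries". Chart abstraction from the TB clinic registries is then described as the method.
- Attribution: "serious adverse events will not be directly attributable to the study". Section 10 repeats this: "serious adverse events (SAEs) will not be directly attributable to the study".
- Source of risk: "The major risks of this screening program are related only to pill-taking mechanisms".

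Section 8.7 gives the matching data step. At the end of the intensive phase a case report form is completed for which "data will be extracted from TB registration logs and participants' charts, focusing on overall treatment outcomes and side effects". The adherence follow-up form in the same section is described as covering daily intake and the reasons for missed doses. No adverse-event question is mentioned.

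Section 8.6 sets the contact schedule. Controls attend on every working day of the intensive phase. Intervention participants come back every 15 days and may consult the provider in between about illness or adverse events, with a telephone number on the appointment card. Both arms have a urine test every 15 days, four per participant (Section 8.7). Section 11.3 has the DSMB review the collected data for safety.

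**The concern.** An event reaches a clinic record only if someone at the clinic learns of it. The trial randomises how often patients meet the clinic, so passive capture from records ties the chance of recording an event to the arm. Daily attendance is also one of the ways in which early or mild toxicity is noticed. An arm that is seen less can show fewer events without having fewer.

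The efficacy outcomes do not rest on these data. What is at stake is the safety picture by arm that goes to the DSMB and later supports a claim that self-administration is an acceptable substitute for DOT. For such a claim, a bias towards self-administration is the unwelcome direction.

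The attribution statement adds to this. Its reason is that the study dictates no diagnosis or regimen. Yet Section 11.2 places the main risk in how pills are taken, and that is what is randomised.

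**Working it through.** **Inputs.** Follow-up is the 60 expected days of Section 9. Control visits fall on every working day and intervention visits every 15 days (Section 8.6). The protocol gives no expected adverse-event rate and no event duration, so durations below are assumptions shown over a range.

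**The plan's own count.** 60 / 15 = 4 assessments, which matches the four urine tests in Section 8.7.

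**Scheduled contacts over 60 days.**

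- Control: 60 × 5/7 = 42.9. Counting by weekday of start gives 42 to 44.
- Intervention: 4.
- Ratio: 42.9 / 4 = 10.7 (range 10.5 to 11.0).

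**Sensitivity of the count.**

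- The eight-week phase of Section 2.1: 56 × 5/7 = 40, and 40 / 4 = 10.0.
- Counting enrolment as an intervention contact: 42/5 to 44/5 = 8.4 to 8.8.
- If controls made only half their visits: about 21 versus 4.

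**From contacts to detection (illustration).** Assume that onset is uniform over days 1 to 60, that an event lasts L days, and that it is recorded only if a scheduled contact falls within it, with no recall and no calls between visits. For L up to 15, the share seen in the intervention arm is 4 × L / 60 = L / 15. In the control arm, any event of three days or more meets a working day unless it is cut off by the end of follow-up; averaged over start days the share is 0.993. At equal true risk, the recorded risk ratio (intervention / control) is (L / 15) / 0.993. Its inverse is the true excess that would look like no difference.

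| Duration L | Control seen | Intervention seen | Recorded ratio at equal true risk | True excess that would look null |
|---|---|---|---|---|
| 3 days | 0.993 | 0.200 | 0.20 | 5.0 |
| 7 days | 0.993 | 0.467 | 0.47 | 2.1 |
| 10 days | 0.993 | 0.667 | 0.67 | 1.5 |
| 15 days | 0.993 | 1.000 | 1.01 | 1.0 |

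This is the extreme case. Anything that lets a provider learn of an event outside a scheduled contact moves the ratios towards 1.

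**The sentences of Section 11.2 side by side.** The reporting sentence covers all adverse and serious adverse events. Two sentences later, capture is limited to what facility records hold, and no other route is described. The attribution sentence settles the general answer before any event, while the risk sentence names the randomised feature as the source of risk. Each pair needs one consistent statement.

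**The case against.** The case on the other side has weight, and several parts of it stand.

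- **Scope of the capture sentence.** It follows directly on the sentence about reactions to TB drugs, so it most naturally refers to those and not to every adverse event. That reading stands. It softens the conflict with the reporting promise but does not remove it, because no separate route for other events is given.
- **Contacts are not detections.** Section 2.1 describes daily DOT as irregular in practice, with little conversation at visits. Section 8.7 allows for some self-administered control doses. Some intervention participants move to daily DOT under Section 8.6. Participants can also report past events at a visit. All of this shrinks the gap, and 10.7 must not be read as a detection ratio.
- **Consultation between visits.** Section 8.6 provides it in order to keep an advantage of DOT. It helps, but it depends on the participant, and no rule says that such contacts are logged.
- **Other safeguards.** Death, non-completion and loss to follow-up form a secondary outcome in both arms, and an independent DSMB reviews safety. The composite misses non-fatal toxicity in people who finish treatment, and the definition of loss to follow-up in Section 8.8.9 describes previously treated patients. The DSMB can review only what was captured.
- **Unseen documents.** The follow-up form, the adverse treatment outcome monitoring tool and the operating procedures are not shown. They may already contain an adverse-event question.

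A reader might also infer that ruling serious events unrelated in advance keeps them out of reporting. The documents do not support that: Section 11.2 requires reporting irrespective of relatedness, so attribution does not act as a filter. Nor do they show that the EFDA promise cannot be kept. The timeline is not stated, and a form completed at month two does not mean that events first become known then. It is fair to say only that the described capture does not secure the promise.

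**Conclusion.** The point holds in a limited form. The capture rule and the visit schedule together make ascertainment unequal between arms, and the likely direction favours self-administration. The effect is confined to short-lived or milder events; those lasting 15 days or more would be met about equally in both arms. The contact ratio of 10.7 is firm for scheduled visits. The recorded ratios of 0.20 to 0.67 for 3- to 10-day events are bounds under the strict assumption that only a scheduled contact reveals an event, and the true distortion is smaller by an amount the protocol does not allow one to estimate.

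It would go too far to say that a safety cost is hidden or that the DSMB will be misled. Deaths, non-completion and losses are collected in both arms, the protocol announces no formal comparison of adverse events by arm, and nothing in it predicts how the DSMB would read the data. The internal tensions in Sections 10 and 11.2 on capture, reporting and attribution are matters of text and do not depend on any assumption.

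**What to change.** 1. Add one identical question on adverse events, serious adverse events and hospital admission, with onset date and seriousness, to the adherence follow-up form, and ask it in both arms at the existing 15-day assessments. Scheduled inquiry is then 4 versus 4. If an unseen form already has such a question, say so in Sections 8.7 and 11.2.
2. Record unscheduled consultations about adverse events on the same form, marked as unscheduled.
3. Tabulate the answers by arm for the DSMB, and show chart abstraction separately as a supplement, so that the extra control visits do not bring the imbalance back.
4. Reconcile the reporting and capture sentences of Section 11.2 by naming the route through which events become known for EFDA reporting.
5. Replace the blanket attribution statements in Sections 10 and 11.2 with case-by-case assessment.

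The cost is a short addition to an existing form, a wording amendment, slightly more form-filling and somewhat higher recorded event counts. No visits or staff are added. The question equalises ascertainment but does not by itself guarantee timely reporting of serious events, since an event could still first be learned of up to 15 days after onset.

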### **11.3. Interim monitoring and analysis**

The investigators will conduct interim monitoring and submit an analysis report to the independent Data and Safety Monitoring Board (DSMB). Then, the report will be sent together with DSMB's recommendation to the IRBs. The DSMB will periodically review and evaluate the study's collected data to follow up participant safety, the accuracy of study procedures, and the study progress in order to provide recommendations on the continuation, modification, or termination of the study. The DSMB will consist of an expert in the clinical aspects of TB, an expert biostatistician, and an investigator with expertise in current clinical trials conduct and methodology. External monitors may conduct technical audits, before, during, and after completion of the trial. This will include reviewing the research protocol, operations manual, standard operating procedures, and training materials before initiation of the trial. The site investigators will make study documents and pertinent records readily available for inspection by the local IRB and site monitors.

## **12. ETHICAL CONSIDERATIONS**

### **12.1. Statement of compliance**

The trial will be carried out in accordance with the International Conference on Harmonization Good Clinical Practice (ICH GCP) and the recently adopted (2018) good clinical trial guideline and requirements of the Ethiopian Food and Drug Administration (EFDA). The investigators have completed Human Subjects Protection and ICH GCP Training. Clinical trial site staff who are responsible for the conduct, management, or oversight of the trial will complete Human Subjects Protection and ICH GCP training.

The protocol, informed consent forms, recruitment materials, and all participant materials will be submitted to the Institutional Review Board (IRB) for review and approval. Approval of both the protocol and the consent form will be obtained before any participant is enrolled. Any amendment to the protocol will be reviewed and approved by the IRB before the changes are implemented in the study. In addition, all changes to the consent form will be IRB-approved; a determination will be made regarding whether new consent needs to be obtained from participants who provided consent, using a previously approved consent form.

## **12.2. Ethical review**

The study does not involve new investigational product and no exemption will be sought. The pillbox device has been in use for clinical purposes other than TB. There will be no change in the treatment of TB from the national guidelines, neither the type of regimen nor the dose, but only the management of treatment.

The proposal and any subsequent modifications will be reviewed and approved by:

- i) Scientific and Ethics Review Committee of the Center for Innovative Drug Development and Therapeutic Trials for Africa, College of Health Sciences, Addis Ababa University;
- ii) Institutional Review Board of the College of Health Sciences, Addis Ababa University;
- iii) Ethiopian Food and Drug Administration Authority (EFDA);
- iv) Ethiopian National Research Ethics Review Committee (NRERC); and
- v) The Institutional Review Board of Addis Ababa City Administration Health Bureau

All study sites will have their permission and written concurrence for data collection

## **12.3. Informed consent**

Study participants, both patients and providers, will be given an information sheet, which includes the purpose of the study, the procedures to be followed, privacy and confidentiality and the risks and benefits of participation. The information sheet will be read to those who cannot read or write in the presence of a witness. All questions about the study will be answered to the satisfaction of the participant. If they agree to be part of the study, they will sign the informed consent. If the participant is illiterate, they will thumbprint the consent form, including the signature of the witness. A copy of the information sheet and the signed consent form will be given to each participant. The interview

questionnaire will be conducted and filled in private. Neither the investigators nor the study provider data collectors will coerce or unduly influence the potential patient to participate or to continue to participate in the study. Participants will have the right to withdraw without any reason for termination or cross-over, and that care will not be affected in any way by declining or participating in the study.

#### **12.4. Confidentiality**

All filled questionnaires, evaluation forms, reports, and other records that leave the study sites will be identified by coded numbers only to maintain subject confidentiality. All records will be kept locked at the principal investigator's study office in Addis Ababa University, CDT-Africa. All computer entry and networking programs will be locked with a password. Participant's information will not be released without written permission of the subject, except as necessary for monitoring by the study team. Only the investigators will have access to the crude data.

#### **12.5. Payment for participation**

There will be no payment for participation, either in cash or in-kind, to patients in the intervention or DOT arm, or healthcare providers, as this would influence outcomes of the study. However, if the participants are coming just for the purpose of the study, they will be reimbursed for transport.
